#### Statistical analysis plan

As some mothers in clusters randomised to the intervention arm may not use the ABHR provided while others in clusters randomised to the comparator arm may acquire an ABHR for themselves, the primary statistical analysis will be by the principle of “intention-to-treat (ITT)”. That is, all mothers and babies will be analysed in the study group to which their village of residence was randomised; this provide appropriate allowance for non-compliance in both groups and produce estimates of intervention effect that are more reflective of what might occur should the provision of an AHBR to new mothers be adopted as a health policy.

Initially, incidence rates of the primary outcome will be compared across the two study arms using generalised estimating equations (GEEs) to allow for clustering effects. A negative binomial distribution and log link function will be used with outcomes in the same cluster assumed to be equally correlated (exchangeable). Effects sizes will be reported as incidence rate ratios (IRRs) with their 95% confidence intervals calculated using robust Huber-White “sandwich” standard errors to correct for any slight misspecification of the correlation structure. Time to the first occurrence of the primary outcome then be analysed in the same way but using Cox proportional hazards regression model with frailty at village level with mothers/babies lost to follow-up included as censored observations. Intervention effects will be reported as hazard ratios with their (robust) 95% confidence intervals. IRR and hazard ratio estimates will be presented both unadjusted and adjusted for important covariates (including age of mother, sex of infant, study hub/geographical area, WASH status (availability of tapped water and type of latrine in dwelling), rural and peri-urban status, highest education level achieved by mother).

All secondary outcome measures will be assessed also using GEE techniques as for the primary outcome, with appropriate distributional assumptions depending on the statistical nature of each measure. Effect sizes will be presented with their (robust) 95% confidence intervals, both unadjusted and adjusted for important covariates. However, to gain some insight into the possible effect of ABHR if adopted fully, a secondary analysis will be performed on a per protocol principle.

Missing baseline covariates will be imputed using simple imputation methods in the covariate-adjusted analysis based on the covariate distributions. For a continuous variable, missing values will be imputed from random values from a normal distribution with mean and SD calculated from the available sample. For a categorical variable, missing values will be imputed from random values from a uniform distribution with probabilities P1, P2, …, and Pk from the sample. For a count data, missing values will be imputed from random values from a Poisson distribution with λ from the sample. Seed for the imputation is set as 128.

Due to the nature of the study, no stopping rules have been set. Any decision to stop the study will be based on a combination of rates of adverse events, recruitment rate, interim data analysis, and the results of other recently published studies. The final decision to stop the study would be made by the trial steering committee.

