**Methods:**

Through a cluster-randomised trial in eastern Uganda, 72 clusters are randomised in a 2-arm design with rural villages as units of randomisation. We estimate to include a total of 5932 pregnant women at 34 weeks of gestation. All women and infants in the study are receiving standard antenatal and postnatal care. Women in the intervention group additionally receive six litres of ABHR and training on its use. Research midwives conduct follow-up visits at participants’ homes on days 1, 7, 28, 42, and 90 after birth and telephone calls on days 14, 48, and 60 to assess the mother and infant for study outcomes. Primary analyses will be by intention to treat.

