#### Trial organisation

For ease of study implementation, the study area is divided into three geographical areas each consisting of a minimum of 24 clusters, each with a study management site (‘hub’) hosted at the largest government run health facility in the area, in Busiu Health Centre (HC) IV, Budaka HC IV, and Kolonyi HC III, respectively. Each hub has a study doctor, village health team members and supervisors, a data manager, at least 7 research midwives to collect data, and 3 staff to train mothers in ABHR use. A cluster is eligible for inclusion in the study if the 1–4 village(s) constituting it have more than 600 inhabitants collectively and if it is not directly neighbouring another cluster (to prevent communication and intervention contamination). The aim is an average cluster size of 850 inhabitants. We surveyed each participating cluster prior to the initiation of the study to determine the population of children under the age of 2 years as a proxy for that cluster’s birth rate. In total, we expect to recruit 5932 pregnant women. Consent was obtained from the leaders of all included villages to approach and recruit mothers potentially eligible for inclusion in the study.

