#### Randomisation

The randomisation process was conducted in each of the three hubs separately and in the presence of representatives from each village within that geographical area. The clusters in each area were listed in order of their population size. The four clusters with the largest populations were labelled “stratum 1”, the next four largest as “stratum 2”, and so on down to the four smallest size clusters (stratum 6). Two red and two yellow balls were put in an opaque cotton bag. The representatives from stratum 1 were called forward and each in turn blindly withdrew one ball without replacement. This process was repeated for the remaining five strata in turn to randomly designate 12 clusters as “red” and 12 as “yellow”. Finally, just one red and one yellow ball were placed in the bag and the eldest of the representatives present asked to blindly withdraw one ball. The clusters designated to the colour of the chosen ball were allocated to the intervention arm of the study and the clusters designated to the colour undrawn were allocated to the comparator arm of the study. The randomisation was thus stratified by geographical area and by population size. [name], a researcher not involved in the day-to-day running of the trial has, kept the final randomisation sequence and will only avail this to the other scientists at the end of trial.

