Should it prove impossible to select 72 village clusters that meet the above selection criteria and have a combined estimate of 5932 births over the study period, additional clusters will be recruited into the study as feasible, to achieve the required sample size. If, however, the projected birth rate across the area covered by the three study areas falls below the required level and additional clusters are needed during the study period, the selection of additional clusters will be carried out in conjunction with the ISDMC. To preserve the balance in the two study arms, clusters will be recruited into a study area in pairs; one cluster in each pair will be allocated to the intervention arm and the other in the pair to the control arm.

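### The Cox model's frailty is placed on villages although clusters of one to four villages were randomised, so the hazard ratio interval may be too narrow

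*Protocol article*

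**What the plan says.** Three parts of the protocol article bear on this.

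- **Trial organisation.** A cluster is eligible "if the 1–4 village(s) constituting it have more than 600 inhabitants collectively", so a cluster may be one village or several.
- **Randomisation.** Clusters are what is allocated: "The clusters in each area were listed in order of their population size". They were then grouped in fours and drawn, giving 12 clusters of each colour per hub.
- **Statistical analysis plan.** The first analysis is a GEE with an exchangeable correlation within cluster and sandwich standard errors. Time to first occurrence is then to follow the same approach, but with a "Cox proportional hazards regression model with frailty at village level with mothers/babies lost to follow-up included as censored observations". Hazard ratios are to carry robust 95% intervals. The grouping unit of that robust variance is not stated for the Cox model.

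The article also uses the word village for the randomised unit. The abstract has "72 clusters are randomised in a 2-arm design with rural villages as units of randomisation". The intention-to-treat paragraph has mothers and babies "analysed in the study group to which their village of residence was randomised". The sample-size text begins a sentence "Should it prove impossible to select 72 village clusters".

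**The concern.** All villages of one cluster receive the same arm and are likely to share local conditions such as health facility, water supply and season of recruitment. A frailty on villages alone treats them as separate independent replicates, so the model counts more units than the 72 that were randomised. Correlation between villages of a cluster then goes unmodelled, and the resulting error has one direction: intervals that are too narrow, not too wide.

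The Cox model addresses the primary outcome and is to be reported both unadjusted and adjusted. If it appeared significant where the GEE did not, a reader could not tell a genuine gain from using event times apart from clustering placed at the wrong level.

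**Working it through.** The article gives no figure for this point, so there is none to reproduce. The check asks how far the standard error falls short if villages are treated as independent.

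**Inputs from the Size determination section**
- 5932 mothers and 72 clusters, so m = 5932/72 = 82.4 per cluster.
- ICC: 0.01 to 0.10 is called realistic, and the power statements use 0.001, 0.005 and 0.01.

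**Assumptions (not in the article)**
- Every cluster has k villages of equal size, m_v = m/k. The article does not report how many clusters have more than one village.
- ρ_v is the correlation within a village, set to the ICC. ρ_c is the correlation between different villages of one cluster, set to half of ρ_v or all of it.
- The design-effect formula approximates the Cox setting.

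**Formulas**
- True design effect = 1 + (m_v − 1)ρ_v + m_v(k − 1)ρ_c
- Village-only design effect = 1 + (m_v − 1)ρ_v
- SE ratio = √(village-only / true)
- Type I error = 2[1 − Φ(1.96 × SE ratio)]

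**Worked case: ICC 0.01, k = 2, all correlation shared.** m_v = 41.19. Village-only = 1 + 40.19 × 0.01 = 1.402. True = 1.402 + 41.19 × 0.01 = 1.814. SE ratio = √(1.402/1.814) = 0.879. Type I error = 8.5%.

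Paired entries are for half / all of the correlation shared.

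| ICC | k | True design effect | Village-only | SE ratio | Type I error, formula | Type I error, simulated |
|---|---|---|---|---|---|---|
| 0.001 | 2 | 1.061 / 1.081 | 1.040 | 0.990 / 0.981 | 5.2% / 5.5% | not run |
| 0.001 | 4 | 1.050 / 1.081 | 1.020 | 0.985 / 0.971 | 5.3% / 5.7% | not run |
| 0.01 | 2 | 1.608 / 1.814 | 1.402 | 0.934 / 0.879 | 6.7% / 8.5% | 6.4% / 8.8% |
| 0.01 | 3 | 1.539 / 1.814 | 1.265 | 0.906 / 0.835 | 7.6% / 10.2% | not run |
| 0.01 | 4 | 1.505 / 1.814 | 1.196 | 0.891 / 0.812 | 8.1% / 11.1% | 7.4% / 9.7% |
| 0.05 | 2 | 4.040 / 5.069 | 3.010 | 0.863 / 0.771 | 9.1% / 13.1% | 8.4% / 13.2% |
| 0.05 | 4 | 3.525 / 5.069 | 1.980 | 0.749 / 0.625 | 14.2% / 22.1% | 12.5% / 21.0% |

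For k = 1, or when villages of a cluster share no correlation, the ratio is exactly 1.

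**Simulation.** The last column comes from 3000 null trials per scenario, with 72 clusters of about 82, 15% event risk and log-normal frailty. A constant-hazard rate model stood in for Cox, with a sandwich variance grouped by village. Near 5%, the Monte Carlo standard error is √(0.05 × 0.95/3000) = 0.4 percentage points. Two further results matter:
- With the variance grouped by randomised cluster, type I error was 4.9–6.2% in every scenario.
- With single-village clusters it was 5.1–5.9%, and the two groupings coincide.

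So a robust variance protects the interval only if it is grouped by the randomised cluster. Grouping it by village leaves the shortfall in place.

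**The case against.** The strongest reply is that this is loose wording. The abstract, the intention-to-treat paragraph and the sample-size text all use village for the randomised unit, and the masking section speaks of allocation by village too. The Cox analysis is introduced as parallel to a GEE that is clustered correctly, and its intervals are to be robust. If that variance is grouped by cluster, a village frailty does no harm to the interval. The article is also condensed, and the full analysis plan, which is not shown, may settle the grouping.

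Much of this stands. A reader might infer that the hazard ratio interval will be too narrow and that its type I error will exceed 5%. The article does not support that: it leaves the variance grouping open, and it does not say how many clusters have more than one village. The larger figures in the table also require every cluster to be multi-village, the higher ICC and most of the correlation to be shared.

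What the reply does not remove is the mismatch itself. The article defines a cluster as possibly several villages, and then uses cluster for the correlated unit of one analysis and village for that of the next. The village is the only unit the Cox sentence names, and it appears where the text says how the Cox model departs from the GEE. Someone programming from a dataset with both identifiers could reasonably follow it to the letter. The point is therefore not a missing detail: a level is stated, and it differs from the randomised unit.

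**Conclusion.** The point holds conditionally. Read literally, the frailty is on a unit smaller than the one randomised. The interval suffers only if three things are true together: some clusters have more than one village, outcomes are correlated across villages of a cluster, and the robust variance is not grouped by randomised cluster.

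At ICC 0.01, with every cluster multi-village, the standard error would be about 7–12% too small for two villages and 11–19% for four. Taking formula and simulation together, type I error would be about 6–9% and 7–11%. At ICC 0.001 the shortfall is at most 3%; at 0.05 it is larger, as tabulated. A mix with single-village clusters lies between these figures and no effect.

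It would be wrong to read this as a flaw in the primary comparison as a whole. The GEE comes first, is clustered on the randomised unit, and is untouched. Only the time-to-event analysis is exposed.

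**What to change.** In the Cox sentence, replace the village-level frailty with a shared frailty for the randomised cluster, and state that the robust standard errors are grouped by randomised cluster. A village term nested within cluster may be added but is not required. A marginal Cox model with standard errors clustered on the randomised cluster would serve equally well. If the full analysis plan carries the same phrase, correct it there too, before the data are analysed by arm.

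The cost is a change of wording and the use of the cluster identifier in the code. Cluster membership is already known from the randomisation, so no new data are needed.

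### Missing baseline covariates are filled by what reads as one marginal random draw under a fixed seed, which slightly weakens the adjusted estimates and ties them to an arbitrary seed

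*Protocol article*

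**What the plan says.** The rule is in the protocol article under Statistical methods, Statistical analysis plan. Its scope is set by "Missing baseline covariates will be imputed using simple imputation methods in the covariate-adjusted analysis based on the covariate distributions". It then gives three cases:

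- Continuous covariates: "missing values will be imputed from random values from a normal distribution with mean and SD calculated from the available sample".
- Categorical covariates: "random values from a uniform distribution with probabilities P1, P2" and so on up to Pk, taken from the sample.
- Count covariates: "missing values will be imputed from random values from a Poisson distribution with λ from the sample".

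The paragraph closes with "Seed for the imputation is set as 128". It mentions no conditioning on other covariates, hub, cluster, arm or outcome, no number of imputed data sets and no pooling step.

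The results affected are named earlier in the same section: "IRR and hazard ratio estimates will be presented both unadjusted and adjusted for important covariates". Adjusted effects are also planned for the secondary outcomes.

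**The concern.** A value drawn from the marginal distribution carries no information about the woman whose value is missing. Entered in the model as if observed, it acts as measurement error, and three things follow. The covariate's coefficient shrinks towards zero. If the covariate differs between arms, the filled-in women no longer show that difference, so the adjustment falls short. And a different seed gives a different adjusted IRR and hazard ratio.

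The second consequence is the one that could matter. Clusters were allocated by a public draw before village representatives (Randomisation), and women are then identified and consented one by one (Identification, recruitment, and study procedures). Differences between arms in education or in water and sanitation (WASH) status are therefore possible, and the adjusted estimates are meant to deal with them.

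This is not detail left to a fuller document: the article states the rule, down to the seed.

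**Working it through.** The article attaches no figure to the imputation, so there is none to reproduce. The check is a short derivation followed by simulation.

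**Derivation.** Let f be the share missing completely at random, β the covariate's log-IRR slope and δ the difference in its mean between arms.

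- Random draw: the filled covariate has about the same variance as the true one, but its covariance with the true one is multiplied by (1 − f). The slope becomes about (1 − f)β. The arm difference in the filled covariate becomes (1 − f)δ. The adjustment made is (1 − f)²βδ instead of βδ, so the share lost is 1 − (1 − f)² = 2f − f².
- Mean fill-in: the slope stays near β and only the arm difference shrinks, so the share lost is about f.
- If δ = 0, there is nothing to lose and no bias arises.

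**Simulation inputs from the article** (Size determination): 5932 women in 72 clusters, 5932/72 ≈ 82 per cluster; comparator rate 15%, reduction 25% (IRR 0.75) and ICC 0.01, all within its power scenarios. The model is a log-link exchangeable GEE with robust standard errors.

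**Assumptions not in the article:** Poisson variance in place of negative binomial; one continuous covariate with log IRR 0.5 per SD; values missing completely at random; arm difference 0 or 0.3 SD. There were 40 data sets per setting and 20 seeds per data set.

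| Missing | Slope relative to full data, draw | Adjustment lost, 2f − f² | Lost, draw (simulated, 0.3 SD) | Lost, mean fill-in | Lost, multiple imputation | SD of log IRR across seeds |
|---|---|---|---|---|---|---|
| 2% | 0.98 | 3.96% | 4% | 2% | 0% | 0.003 |
| 5% | 0.95 | 9.75% | 10% | 4% | 0% | 0.004–0.005 |
| 10% | 0.90 | 19% | 19% | 9% | 0% | 0.006 |
| 20% | 0.79–0.80 | 36% | 38% | 20% | 2% | 0.007 |

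Multiple imputation here used a model with arm and outcome and 10 draws, with the estimates averaged.

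**One row in full** (10% missing, 0.3 SD). The IRR is 0.746 with full data, 0.865 unadjusted, 0.767 with the draw and 0.756 with mean fill-in. On the log scale these are −0.293, −0.145, −0.265 and −0.280. The full adjustment is 0.148. The draw falls short by 0.028, and 0.028/0.148 ≈ 19%. Mean fill-in falls short by 0.013, and 0.013/0.148 ≈ 9%. The standard error is about 0.085, so the draw's shortfall is about a third of it.

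**Balanced arms, 10% missing.** The mean adjusted IRR is 0.750 with full data and 0.750 with the draw.

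**Seed dependence.** The SD across seeds is 3 to 9% of the standard error. At 10% missing the IRR spans about 0.017 over 20 seeds. Significance at 5% changed with the seed in 0 to 10% of data sets, depending on the setting.

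**Second simulation** (binary covariate with risk ratio 2, 10% risk, ICC 0.01). The SD across seeds was 0.002 to 0.003. The RMS deviation of the log IRR from the complete-data fit was 0.006 at 10% missing and 0.012 at 25%, against 0.004 and 0.007 for mean fill-in plus an indicator.

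**The case against.** The strongest reply is that this will change nothing. At 10% missing, the SD across seeds is about 0.006/0.085 = 7% of a standard error, and balanced arms show no bias. High missingness is also doubtful for most of the covariates listed. Hub and rural or peri-urban status follow from residence, age bears on eligibility, and infant sex can be seen at the postnatal visits. That leaves mainly education and WASH status. All of this stands, and it limits the size of the point. The covariate list is open-ended, however, and the only loss rate the article gives (2% in the pilot) concerns follow-up, not covariates.

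A second reply is that a pre-specified seed is good practice, because it prevents choosing among seeds, and that multiple imputation needs one too. That also stands. But fixing the seed makes one arbitrary answer repeatable; it does not make the answer less arbitrary. Averaging over draws does.

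Some stronger readings are tempting but not supported:

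- *The trial's main result is compromised.* The article reports unadjusted and adjusted estimates side by side and does not put the adjusted one first. The unadjusted one is unaffected.
- *The categorical rule contradicts itself.* A uniform distribution does not have unequal probabilities, but cutting uniform random numbers at cumulative sample proportions is a standard way to draw a category. The sentence is loose with one evident meaning.
- *An unbounded normal will produce impossible maternal ages.* The article gives no mean or SD for age, so this cannot be shown.
- *The arms do differ.* Recruitment after a public draw makes this plausible, but nothing shows it. The 0.3 SD is an assumption.

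**Conclusion.** The point holds as a minor one. The stated rule is inferior to simple alternatives and offers no advantage over them. It shrinks the covariate's coefficient by about the missing share and adds a small seed dependence to the adjusted estimates (SD of the log IRR about 0.002 to 0.007). It matters beyond that only if a covariate such as education or WASH status is often missing and also differs between arms: about 19% of the adjustment is lost at 10% missing under the assumed 0.3 SD difference, and about 4% at 2% missing.

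This rests on reading the rule as a single draw, which is inferred from its being called simple, the single seed and the absence of pooling. It also rests on values missing completely at random and on one moderately prognostic covariate. Only the IRR was simulated; the same mechanism applies to the hazard ratio, but its size was not computed. Interval coverage was not checked, and no claim is made about it.

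**What to change.** Replace the imputation paragraph before outcome data by arm are examined:

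- Delete the normal, categorical and Poisson random-draw rules.
- Where missingness in a covariate is more than minimal, use multiple imputation from a model that includes arm, outcome, hub and the other covariates. State the number of imputations, pool the estimates, and fix a seed for reproducibility.
- Where it is minimal, use deterministic mean fill-in computed without regard to arm, with a missing category or indicator where numbers allow.
- Set the boundary between the two in advance.
- If any categorical draw is kept, describe it as a draw from a categorical distribution with the sample proportions.

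The cost is one reworded paragraph and a little more analysis work for multiple imputation. Design, data collection and sample size do not change. There are trade-offs. Under imbalance, mean fill-in with an indicator still loses about half as much adjustment as the random draw (10% against 19–20% at 10% missing, with a 0.3 SD difference), so it should not be the only method. Missing categories may also be sparse when few values are missing.
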